**Figure 3. F3:**
[figure not shown]
Study design of the “My Life” intervention. Green indicates data related to study 1, yellow indicates data related to study 2, and purple indicates data related to study 3. Student- and system-level data related to studies 1 and 2 are collected in both intervention and control schools, whereas data related to study 3 is collected in intervention schools only HPS: health promoting school.

**Table 2. T2:** Overview of data collection activities, timing, purpose, and analytical strategy.

Research objective, focus, and data collection activities	Timing	Purpose	Analytical strategy
1. Student-level outcomes			
Student surveys will be collected at baseline (T0; n≈416); approximately 2‐3 months later at mid-intervention (T1; n≈500), and approximately 4 months after that at follow-up (T2; n≈500)	August 2025-May 2026	To estimate effect changes in student mental and physical health and school well-being	Multilevel mixed models
2. System-level outcomes			
Health promoting school practice and capacity surveys collected among school staff at two time points (n≈70)	April-August 2025; May 2026	To describe differences in school staff health promotion (HP) practices	Pre-post test
Semi-structured interviews with school and municipality coordinators, and school and municipal managers (n=16)	April-June 2026	To identify systems impacts and map system activities, unanticipated outcomes and trace causal pathways across the school systems	The water of systems change [59]; Partnership Synergy Theory [60]
3. Implementation			
Short interviews with health consultant coordinators about the preparation and planning phases	August 2025	To assess implementation degree (high, medium, or low) for each intervention site	
Surveys administered after each health education session and anchoring meetings to health consultants	August-January 2025	To assess fidelity and acceptability of delivering “My Life”	Implementation outcomes [61,62]
3. Mechanisms			
Observations of health education sessions focusing on student engagement (n=20)	August-November 2025	To explore mechanisms of change at the student level	Realist-informed thematic analysis [63]
Semistructured FGIs^a^ with students across all four schools (n=4) and follow-up FGIs (n=4)	November-December 2025	To explore mechanisms of change at the student level	Realist-informed thematic analysis [63]
Semistructured interviews with school and municipality coordinators, and school and municipal managers (n=16)	May-June 2026	To explore mechanisms of change at the system level	CMO^b^-based deductive coding [59,60]

a FGI: focus group interview.

b CMO:context mechanism outcome.

### Matching and Assignment of Schools to Intervention and Control Schools

Before initiation of the “My Life” partnership, Vallensbæk municipality collaborated through the regional partnership “Cope with Life – Without Smoke and Drugs” [64] focused on adolescent health promotion. This partnership provided a practical framework for recruitment. Schools were recruited using convenience sampling, as participation was primarily limited to municipalities and 10th-grade schools already in the partnership. Through this partnership, 9 municipal 10th-grade schools were approached. Vallensbæk Municipality, which had implemented an earlier version of “My Life” for 5 years, served as the pilot school of the fully developed intervention. Of the remaining 8 schools, 7 agreed to participate following introductory meetings, while one declined due to a lack of interest. To balance intervention and control schools and account for anticipated student dropout, an additional control school from the region was recruited. During intervention development, randomization of schools was deemed unfeasible due to practical and organizational constraints, including partnership-based implementation context and differing readiness among schools to implement the intervention during 2025-26 or 2026-27. This is consistent with recommendations supporting nonrandomized designs when highly controlled conditions are not feasible [51]. Instead, schools were matched based on (1) their number of students and classes; (2) contextual and sociodemographic factors (including percentage of students with Danish ethnic backgrounds and average grades in mandatory exams); and (3) readiness to implement the intervention during the school years 2025-26 and 2026-27. Because schools were not randomized, baseline differences between intervention and control schools are expected. To assess potential selection bias, baseline student characteristics and school-level contextual characteristics will be examined descriptively across groups. Relevant baseline covariates, including gender, socioeconomic indicators, migration status, and school-level contextual factors, will be included in the mixed-effects analyses where appropriate. Four intervention schools with 11 classes were matched with 4 control schools with 15 classes. All enrolled 10th-grade students in participating classes were eligible to participate in the effectiveness trial, except students who could not read and understand Danish. All students were eligible to receive the intervention.

Because the study was implemented within an existing municipal partnership structure, the sample size was determined pragmatically by the number of participating schools eligible for implementation during the study period. Based on expected enrollment across the 8 schools, approximately 416 students are expected to participate. Although no formal a priori power calculation was performed during intervention development, sample size considerations were informed by comparable school-based quasi-experimental studies targeting adolescent health literacy and school well-being outcomes, which have demonstrated statistically significant intervention effects with similar sample sizes [65]. The study should therefore be considered adequately powered to detect small-to-moderate intervention effects at the student level, while acknowledging that statistical power for school-level effects may be limited due to the relatively small number of schools.

### Study 1: Effectiveness Evaluation at Student Level

#### Methods

The evaluation of student-level effectiveness will examine whether the intervention improves students’ positive mental and physical health and school well-being. This section describes the methods used to evaluate effectiveness within the pragmatic controlled trial design using repeated questionnaire measures collected at baseline and follow-up time points.

#### Primary Student-Level Outcomes

Positive mental health is operationalized through three aspects: social and emotional competences, self-efficacy, and mental well-being. These reflect both the hedonic perspective (mental well-being) and the eudaimonic perspective (social and emotional competences and self-efficacy) [66]. Social-emotional competence is measured using an index originally developed and tested for fifth to ninth-grade students [31], which covers three aspects—assertiveness, empathy, and collaborative skills. Self-efficacy is measured using a scale from the Danish Health Behavior in School Children (HBSC) which has been face-validated among students in grade 5‐9 [67]. Finally, mental well-being is measured using the validated shortened version of the Warwick-Edinburgh Mental Well-being Scale (WEMWBS) [68]. Physical health is measured using health literacy as both an indicator and determinant of health [69]. This is measured using the validated Danish version of the Health Literacy for School-aged Children (HLSAC) instrument, which covers five aspects: theoretical knowledge, practical knowledge, critical thinking, self-awareness, and citizenship [70]. School well-being is measured covering three aspects: positive student interpersonal relations, positive student-teacher relations, and school connectedness using items from the HBSC [71]. Student interpersonal relations are assessed using a student support scale, and student-teacher relations are assessed using a teacher-relatedness scale (ibid). Both scales have shown adequate validity and reliability in samples of 13- and 15-year-old students [72]. School connectedness is measured using a connectedness scale from the HBSC, which has shown good internal reliability in a subsample of Danish schoolchildren aged (11‐13 y) [45].

#### Secondary Student-Level Outcome

For secondary student outcomes, grouped under physical health, we will assess health behavior during school hours: (1) physical activity, which is measured using two items; (2) smoking and nicotine use, which is measured using 2 items; and (3) social media use, which is measured using one item. In addition, we will assess aspects of food literacy, using 3 adapted items of the validated Food Literacy Questionnaire [54].

#### Student Characteristics

At baseline, the following individual characteristics are collected: gender, age, migration status (with items on student and parental place of birth), and socioeconomic status (with items on parental employment and occupation), based on the standardized HBSC survey [11]. Moreover, family social structure is measured with 2 items [73], and language spoken mostly at home is measured with one item. Perceived social support is measured with one item on having someone to talk to when experiencing problems [74], and perceived school pressure is measured with one item on school-related pressure [11].

#### Data Collection

The indicators and research procedures were pilot tested during the school year 2024-25 through baseline and follow-up questionnaires and student focus group interviews (FGIs) (n=11) conducted in Vallensbaek municipality.

In the main trial, outcomes are measured through student surveys administered at 3 time points. Baseline data were collected in September 2025, approximately 4 weeks after the summer break. This timing was chosen based on findings from the pilot study, where students indicated that they needed more time in 10th grade to respond accurately to the questionnaires. A mid-intervention measurement (Time 1, T1) was collected immediately after the completion of the health education program (2 to 3 months after baseline). A follow-up measurement (Time 2, T2) will be collected approximately 7 to 8 months after baseline, allowing time to implement health promotion actions during the anchoring phase while remaining prior to the examination period (see Table 2, which outlines data collection for all 3 research objectives).

Data from intervention and control schools were collected concurrently. Student surveys were administered in schools during a 45-minute class session. Students were guided via video and instructed to wear headphones during the session. Researchers and trained interns supervised the class, supported technical issues, and prevented student interaction.

#### Analysis Plan

Scale validation will be conducted for the 3 constructs of positive mental health (self-efficacy, social and emotional competences, and mental well-being), 3 constructs of school well-being (positive student interpersonal relations, positive student-teacher relations, and school connectedness), and health literacy using Cronbach alpha to assess internal consistency. Intervention effects will be evaluated by mixed-effects modeling following the intention-to-treat principle. Data will be analyzed for each primary outcome separately, using models that account for the hierarchical school-based data structure, including repeated measurements within students and clustering of students within classes and schools. Random effects will be specified at relevant levels, where supported by the data, and the final random-effects structure will be selected based on the study design, data structure, model fit, and convergence. The effect will be estimated separately for each outcome with a group (intervention/control) × time interaction term, with time specified as a categorical variable with 3 levels (baseline, T1, and T2). The primary hypothesis for each outcome specified in the program theory concerns the comparison between the groups at T2, where the full intervention is implemented. All statistical tests will be 2-tailed, with the level of statistical significance set at *P*<.05. Each model will adjust for baseline values of the outcome and relevant confounders. Because the study is nonrandomized, baseline characteristics will be compared descriptively between intervention and control groups, and relevant baseline imbalances will be considered in the adjusted models where appropriate. Missing data will be described by group and time point. Mixed-effects models will use all available data under standard likelihood-based assumptions, and the potential impact of missing data will be considered when interpreting the findings. Model assumptions and graphs will be checked prior to analysis.

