### Study Design

Evaluating system-oriented HPS interventions such as “My Life” is challenging due to their multiple target groups, settings, and phases implemented at different organizational levels [51]. Consequently, the evaluation requires multiple context-adaptable designs and methods to address the 3 research objectives [51] (Figure 3). The different designs address the distinct research questions and are analytically complementary, capturing effectiveness, system-level impact, and implementation processes [53]. The evaluation encompassing all 3 research objectives will take place from January 2025 to June 2026. The effectiveness trial (study 1) follows a pragmatic controlled waiting list design with the participating schools as the assigned unit of allocation. Pragmatic trials are designed to determine intervention effects under real-world conditions rather than highly controlled efficacy trials [54]. The design and reporting of the trial are informed by the CONSORT (Consolidated Standards of Reporting Trials) extension for pragmatic trials. Schools are assigned to intervention either in 2025-2026 or 2026-2027. Schools scheduled to receive the intervention in 2026-2027 serve as controls in the trial. The system impact evaluation (study 2) and process evaluation (study 3) acknowledge that HPS interventions are context-bound and are approached through system thinking and realist evaluation. These approaches provide nuanced insights relevant for discussing potential scalability and for understanding outcomes and effects beyond the individual level (Bonell et al [55]: will it work here and for whom?). System-level impact (study 2) is evaluated through a mixed-method design inspired by Pinzon et al [56], while implementation processes at intervention schools (study 3) are examined using an adaptive multimethods design informed by realist evaluation [57], systems thinking [58], and guidance for developing and evaluating complex interventions [51]. The specific methods, data collection, and data analysis used to answer the 3 objectives are explained in detail below and illustrated in Table 2.

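### The random-effects rule lets the school level be removed after the data are seen, although schools were allocated and there are only four per arm

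*Protocol article*

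**What the plan says.** The Study Design section describes a controlled waiting-list trial "with the participating schools as the assigned unit of allocation". The section on matching and assignment reports that "Four intervention schools with 11 classes were matched with 4 control schools with 15 classes" and that "approximately 416 students are expected to participate".

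The Study 1 Analysis Plan promises models that account for the data hierarchy, "including repeated measurements within students and clustering of students within classes and schools". It then makes the random part conditional: "Random effects will be specified at relevant levels, where supported by the data". On how the choice is finally settled, the same sentence adds that "the final random-effects structure will be selected based on the study design, data structure, model fit, and convergence". No sentence says that the school level stays in regardless of fit.

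Time is a three-level factor that includes baseline, and the effect is a group × time interaction. Each model also adjusts for the baseline value of the outcome. On the target, "The primary hypothesis for each outcome specified in the program theory concerns the comparison between the groups at T2"; on the error rate, "All statistical tests will be 2-tailed, with the level of statistical significance set at *P*<.05".

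**The concern.** Between-school variation belongs in the standard error because whole schools were assigned, whether or not the data demonstrate it. Eight schools leave 8 − 2 = 6 between-school degrees of freedom, so a modest school variance will often fail a fit criterion or be estimated at zero. A rule that rewards fit and convergence puts at risk the one term that the design requires.

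What is at stake is the 5% error rate and the width of the intervals for the T2 comparison on each primary outcome. The random structure could also differ between outcomes for reasons seen only in the data. The sample-size discussion connects the small number of schools with power, not with false positives.

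**Working it through.** The article gives no ICC, variance or type I error figure, so there is no stated figure to reproduce.

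**Inputs from the article.** 4 + 4 schools; 11 + 15 = 26 classes; about 416 students, so 416/26 = 16 per class; 11 × 16 = 176 intervention and 15 × 16 = 240 control students; two-sided 5%.

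**Assumed.** Total variance 1; school ICC 0 to 0.10; class ICC 0.02 (0.05 as a check); equal classes; complete data; classes per school 3, 3, 3, 2 against 4, 4, 4, 3.

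The article combines a group × time interaction with adjustment for baseline, so the T2 test can be read in two ways.

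**Reading A: baseline-adjusted comparison at T2.** The model is outcome = group + school + class + student error, with no true effect. There were 3,000 simulated trials per setting, giving a Monte Carlo standard error of √(0.1 × 0.9/3000) ≈ 0.5 points at a 10% rate. Fits were by REML with the student-level variance taken as known. School was dropped when the likelihood-ratio statistic for school + class against class only was below 2 (the AIC rule). The t references used 24 df if school was dropped and 6 df if it was kept.

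| School ICC (class ICC 0.02) | 0 | 0.01 | 0.02 | 0.03 | 0.05 | 0.10 |
|---|---|---|---|---|---|---|
| School variance estimated as zero | 59% | 39% | 27% | 18% | 9% | 3% |
| School dropped by AIC | 95% | 85% | 73% | 61% | 43% | 18% |
| Type I, AIC selection, normal | 5.4% | 8.3% | 9.9% | 11.1% | 11.0% | 11.6% |
| Type I, AIC selection, t | 4.2% | 6.6% | 8.4% | 9.1% | 8.3% | 7.8% |
| Type I, school always kept, normal | 4.6% | 6.4% | 7.5% | 8.8% | 8.5% | 10.3% |
| Type I, school always kept, t with 6 df | 1.3% | 2.3% | 3.8% | 4.2% | 4.1% | 5.3% |
| Type I, t-test on 8 school means | 5.0% | 5.0% | 5.3% | 5.0% | 5.1% | 5.5% |

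With class ICC 0.05 and school ICC 0.02 or 0.05, AIC drops school in 78% or 52% of trials, and type I error with a normal reference is 9.2% or 11.8%.

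**Reading B: group × time contrast as change from baseline.** With complete data, school, class and student random intercepts cancel from the change. Keeping or dropping the school intercept then makes no difference; what matters is a school × time term. Take residual variance 0.4 per occasion and let v be the school × time variance per occasion, with schools weighted equally within arm.

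- Variance the intercept-only model reports: 2 × 0.4 × (1/176 + 1/240) = 0.0079.
- Variance it misses: 2 × v × (1/4 + 1/4) = v.
- Type I error: 2 × [1 − Φ(1.96 × √(0.0079/(0.0079 + v)))].

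| v | Effective critical value | Type I error |
|---|---|---|
| 0.0025 | 1.71 | 8.8% |
| 0.005 | 1.53 | 12.5% |
| 0.01 | 1.30 | 19.3% |
| 0.02 | 1.04 | 29.7% |

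Some school × time variation is plausible on the article's own account. The programme is adapted locally, anchoring actions are developed school by school, T2 is timed to leave room for them, and the Potential Challenges section expects implementation to differ between schools.

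**The case against.** A reader might infer that the school term will be dropped, and that the 5% level therefore fails for every primary outcome. The article does not support that. Study design and data structure stand beside fit and convergence in the rule, and the preceding text commits to clustering within schools, so the authors may well keep the term. The text permits removal; it does not direct it. The true ICC is unknown, and at school ICC 0 dropping school does no harm. School-level covariates, which the article allows, could also reduce the residual school variance.

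The article names neither AIC, nor a normal reference, nor an intercept-only model; these are assumptions of the calculation. Part of the inflation comes from the normal reference alone: a school term that is always kept still gives 6.4% to 10.3% at school ICC 0.01 to 0.10. The degrees-of-freedom method may properly sit in an analysis plan that is not shown, so its absence is not held against the article.

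It is also tempting to add the two sets of figures together. That would be wrong: where intercepts cancel, losing the school intercept does not affect the contrast.

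What stands is that the article itself states a data-dependent rule and protects no level from it. With t references, selection by fit still gives 6.6% to 9.1% at school ICC 0.01 to 0.05, so the reference distribution is not the whole explanation.

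**Conclusion.** The point holds as a flaw in a stated rule: the plan allows the level at which allocation took place to be removed after the data are seen, with too few schools for non-detection to be informative.

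The size is conditional. Under Reading A, type I error is about 8% to 11% with a normal reference, or 7% to 9% with t references, for school ICC 0.01 to 0.05 and class ICC 0.02 if AIC makes the choice. Under Reading B it is about 9% to 30% for an unmodelled school × time variance of 0.25% to 2% of the total, given residual variance 0.4, intercepts only and a normal reference. One reading or the other applies, not both. The point concerns the error rate only and is separate from selection bias due to non-random assignment.

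**What to change.** Before T2 outcomes are analysed, state in the analysis plan that:

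1. The school level is retained in every primary model on design grounds, whatever the fit. If the tested contrast is change from baseline, school × time is retained too. Only lower-level terms may be simplified to obtain convergence.
2. The T2 contrast is tested with a small-sample reference (Kenward-Roger or Satterthwaite), with at most about 6 between-school degrees of freedom and fewer if school-level covariates are used.
3. An analysis of the 8 baseline-adjusted school means is reported for every primary outcome. Switching to it only when the model is singular would be another data-dependent choice, and a likely one: the school variance alone is estimated as zero in 9% to 39% of trials at school ICC 0.01 to 0.05.

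The change is to wording only. The price is wider intervals: with 6 df the critical value is 2.45 rather than 1.96, a factor of 2.45/1.96 = 1.25 before any change in the standard error. The mixed-model test is also somewhat conservative if the school ICC is very small (about 2.3% at 0.01).

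### Baseline is both an outcome level and a covariate in the same mixed model, so the stated adjustment barely touches the group × T2 effect

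*Protocol article*

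**What the plan says.** In the Protocol article, Study 1, Analysis Plan, the effect on each primary outcome is estimated with a "group (intervention/control) × time interaction term, with time specified as a categorical variable with 3 levels (baseline, T1, and T2". Baseline scores are therefore rows of the outcome. The models are mixed models, "including repeated measurements within students and clustering of students within classes and schools". On the contrast of interest the plan states: "The primary hypothesis for each outcome specified in the program theory concerns the comparison between the groups at T2". The same paragraph adds: "Each model will adjust for baseline values of the outcome and relevant confounders". On missing data it says: "Mixed-effects models will use all available data under standard likelihood-based assumptions".

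The paragraph does not say that baseline rows are dropped when baseline is a covariate, that the two groups share a common baseline mean, or that any covariate interacts with time.

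The section on matching and assignment of schools says that randomisation was not feasible and that baseline differences are expected. It names gender, socioeconomic indicators, migration status and school-level factors as covariates for the mixed models.

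**The concern.** The two sentences describe two different models. A three-level time factor with a group × time term is a difference-in-change model, in which baseline is an outcome. Adjusting for the baseline score belongs to a model in which baseline is a covariate and only T1 and T2 are outcomes. Merged, they give a model in which the adjustment does not do what the text implies.

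The schools were not randomised, and covariate adjustment is one of the plan's answers to the imbalance it expects. If the effect is the interaction, it would be reported as adjusted for baseline and confounders while being essentially the unadjusted difference in change. If the effect is the group difference at T2 from the same model, adjustment does move it, but through a distorted baseline slope and an understated residual variance. The plan does not say which quantity is meant. The sensible repairs give materially different answers when groups differ at baseline, so leaving the choice until the data are seen is a risk for every primary outcome.

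**Working it through.** The article gives no figure to reproduce here. The check is algebra, then simulation on assumed inputs.

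**Inputs from the article.** 416 students; 11 intervention and 15 control classes; three time levels; two-sided 5% tests.

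**Assumed inputs.** 416 / 26 = 16 students per class, so 11 × 16 = 176 against 15 × 16 = 240. Scores are in SD units.

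**1. The interaction.** Write student i's score at time t as μ_t + γG_i + δ_tG_i + βb_i + θx_i + (student, class and school intercepts) + e_it, where b is the baseline score and x a confounder. Then

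y_i2 − y_i0 = (μ_2 − μ_0) + δ_2G_i + (e_i2 − e_i0).

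The terms βb_i and θx_i and all the intercepts have gone. With complete data the estimate of δ_2 is the raw difference in mean change.

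Simulation check: student and class random intercepts, 40 replicates; assumed baseline gap −0.3, T2 effect 0.2, within-student variance 0.4, one confounder imbalanced by 0.4 SD. Mean group × T2 estimates:

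| Covariates (main effects) | Complete data | About 20% missing at T1/T2 |
|---|---|---|
| none | 0.1926 (SE 0.0882) | 0.2020 |
| confounder | 0.1926 (SE 0.0882) | 0.2021 |
| confounder + baseline | 0.1926 (SE 0.0882) | 0.2014 |

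With complete data the discrepancy in any replicate was below 1e-15. With missing data the largest shift in one replicate from adding both covariates was 0.028, against an SE of about 0.098. Adding confounder × time terms to the complete data did move the coefficient, by up to 0.033 in one replicate.

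**2. What this leaves open.** If the arms differ by 0.4 SD in a socioeconomic measure and that measure carries a trend of 0.2 SD per SD, the interaction keeps a bias of 0.4 × 0.2 = 0.08 SD with or without the main effects. Both inputs are illustrative.

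**3. The other reading: group + group × T2.** Assume unit variances, correlation r = 0.6 between all waves, a random-intercept fit and no clustering.

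- Common baseline slope: (1 + 2r)/3 = 2.2/3 = 0.733. The slope of T2 on baseline is 0.60.
- True residual variance at T2: 1 + 0.733² − 2 × 0.733 × 0.6 = 0.658.
- Residual variance of the baseline rows: (1 − 0.733)² = 0.071.
- Variance the model uses: (0.071 + 2 × 0.658)/3 = 0.462.
- True SE / model SE: √(0.658/0.462) = 1.19. The model SE is 1/1.19 = 0.84 of the true one, about 16% too small.
- Type I error: 2 × [1 − Φ(1.96/1.193)] = 0.100.

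A simulation of 4,000 null datasets under these assumptions gave slope 0.733, empirical SE 0.081 against model SE 0.067, and 10.3% rejections.

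In the simulation of step 1 (complete data), adding the baseline covariate cut the student variance from 0.56 to 0.06 and shrank the fitted baseline gap from −0.32 to −0.09. The T2 difference was −0.01 unadjusted, −0.12 with the confounder, and 0.11 with confounder and baseline.

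**4. Does the choice matter?** Same complete data, mean T2 effect:

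- group × T2 as written, or baseline as outcome only with free group means: 0.193 (SE 0.088)
- baseline as outcome only, common baseline mean, confounder included: 0.119 (SE 0.083)
- baseline as covariate only: 0.064 (SE 0.086)

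**The case against.** **The interaction already removes stable group differences.** This stands. The group × time term takes out any constant additive gap between groups, measured or not, and the schools were also matched on size, sociodemographic context and readiness. A reader might infer that the trial has no defence against confounding. The documents do not support that. What stays unaddressed is a difference in trend that goes with the covariates.

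**The adjustment is not literally without effect.** This also stands. Exact cancellation needs complete data and main-effect covariates, and it was checked for random intercepts only, whereas the plan leaves the random-effects structure open. Confounder × time terms are not excluded by the text, though none is stated.

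**The inflated type I error does not belong to the stated effect term.** Correct. It applies to group + group × T2, at r = 0.6 and without clustering. With an assumed class intraclass correlation of 0.05 and class intercepts fitted, 120 null replicates rejected 3.3% for the interaction and 6.7% for the T2 contrast. A true rate of 10% has Monte Carlo error √(0.1 × 0.9/120) = 2.7 points in such a run, so 6.7% settles nothing for the T2 contrast. The run shows no inflation for the interaction.

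**Baseline as covariate is not plainly the better primary model.** This stands. With a stable gap of −0.3 SD and no effect, difference in change gives 0.00, while the baseline-covariate model gives −0.3 × (1 − 0.6) = −0.12 SD. That model also cannot use students without a baseline survey unless they are imputed. Table 2 lists about 416 students at baseline and about 500 at T1 and T2, so that group may not be small.

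**The sentence may be loose shorthand in a condensed article.** Possibly, but it is a positive statement about every primary model and conflicts with the time coding beside it. It needs correcting, not just more detail.

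**Conclusion.** The point holds. The plan gives baseline two incompatible roles. On the ordinary reading of adjustment, the group × T2 effect equals the unadjusted difference in change with complete data and stays very close to it with about 20% missing. The stated adjustment therefore does not deal with covariate-related differences in trend between groups that were not randomised. The alternative T2 contrast is over-adjusted (slope 0.73 instead of 0.60) and can carry too small a standard error.

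The result for the interaction rests on main-effect covariates and random intercepts. The 16% and 10% figures rest further on r = 0.6, equal correlations between waves and no clustering. The article supplies none of these, so they illustrate the mechanism and do not predict this trial's error rate.

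Two stronger conclusions should not be drawn. One is that the trial's primary test has a doubled false-positive rate: the stated effect term is the interaction, which shows no such inflation. The other is that baseline as covariate must be the primary model: in a non-randomised design that choice is contested, and nothing in the article settles it.

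**What to change.** Delete the combination and fix one specification before analysis.

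- **(a)** Keep three-level time and all available data, remove the baseline-outcome covariate, and add confounder × time terms for gender, socioeconomic status and migration status, and for school-level factors where eight schools allow it. The primary contrast is group × T2.
- **(b)** Use T1 and T2 only as outcomes, with group × time, baseline × time and confounder × time. The primary contrast is the adjusted group difference at T2. State how students without a baseline survey are handled.

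Give the reason for the choice, since the two estimate different quantities when groups differ at baseline, and report the other as a sensitivity analysis.

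The cost is rewording, a few extra parameters and one extra analysis. No new data are needed. Option (b) additionally needs imputation for students with no baseline survey, or loses them from the primary analysis.
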